### Cost-effective analysis

For the determination of cost-effectiveness, we will follow the WHO’s guidance on the economic evaluation of TB interventions [50]. To this end, we will determine the incremental costs per additional DALY averted per percentage increase in treatment success. All costs and DALYs derived from the models will be discounted at 3%, and a 5-year horizon will be used. The price year used will be the first year of research implementation, and a discount rate of 3% shall apply. We hope that this intervention will be scaled up if it shows clinical effectiveness. Therefore, we model the overall programmatic cost of implementing the intervention at scale.

We will use the societal perspective to determine the cost-effectiveness of the intervention, assuming government standard rates and costs. From the financial records of the project, we will abstract disaggregated data on the costs (prevailing dollar rate in the year of implementation) of direct financial costs (micro-costing). To determine the direct costs for scale-up, we will exclude costs related to conducting research that would otherwise not be met if the intervention is implemented according to government standard cost.

We then model the cost-effectiveness of the intervention by assuming 72% and 100% phone coverage in patients with TB. We will construct a decision-analysis model using TreeAge® software (version 3.5, MA, USA) to compare the cost-effectiveness of digital intervention versus standard of care. The probabilities of cure and treatment completion to be used in the software will be obtained from the study (for intervention) and national TB reports (for control arms). We will use the national TB prevalence survey [38] to estimate the number of patients with TB nationally. The years of life lost (YLLs) averted will be calculated by subtracting the median age at death from TB from the estimated average life expectancy at birth for Uganda. Regarding the determination of YLL for HIV co-infected patients, a Markov model for ART-experienced PLHIV will be fitted. The global burden of disease estimates will be used to determine the disability-adjusted life years (DALYs) weights for those patients with TB and life expectancy at birth [51].

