### Research objectives

The primary objective of this study is to determine the impact of an IVRT software (CFLU-TB) on treatment success in patients receiving treatment at public facilities in Uganda. The secondary objectives were as follows:
To compare TB cure rates (six months) in patients with microbiologically diagnosed TB in the intervention and control arms.To compare treatment completion (six months) in patients clinically diagnosed with TB in the intervention and control arms.To determine the effect of enhanced TB treatment support with CFLU-TB on retention at 2 and 6 months in patients receiving TB treatment.To assess the perception of patients’ care providers (treatment buddies) and other stakeholders about CFLU-TB.To determine the cost-effectiveness of the intervention.To compare adherence rates between patients in the intervention arm and control arms.To determine the effect of CFLU-TB on adherence to clinic appointments.To compare knowledge about TB/HIV in patients enrolled in the intervention and control arms.To determine Drug-resistant TB rates in the intervention and control arms.To determine the uptake of the CFLU-TB tool in patients and their care providers (treatment buddies).

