### Trial endpoints

The primary endpoint is treatment success (at 6 months): treatment success is a composite outcome, comprising treatment completion and cure in patients with clinically and bacteriologically diagnosed TB, respectively. It is a robust and agreed indicator of treatment success in TB programs. In patients with bacteriologically diagnosed TB, cure is defined as having a negative sputum test in the last month of treatment and on at least one previous occasion [47]. For clinically diagnosed patients, completion entails 6 months of therapy. The denominator for each arm will be the number of patients enrolled. At the same time, the numerator is the sum of bacteriologically and clinically diagnosed patients with cure or treatment completion, respectively.

This RCT also has several secondary endpoints. First, we will determine the TB cure rates in patients with microbiologically diagnosed TB. Second, we will determine treatment completion for patients clinically diagnosed with TB in the two arms: Third, retention rates will be determined and compared between the study arms. Patients will be deemed to be actively engaged in care if they attend a clinic visit within one month of a scheduled appointment. Additionally, we will compare appointments. We will categorize visits as “early,” if they present before an appointment, “prompt” if they show up within three days after the appointment date, “late” if they present after three days but within 30 days of a scheduled appointment and missed if patients do not show up at all or present after 30 days. Fourth, we will determine the incremental costs per additional DALY averted per percentage point increase in treatment success in the intervention versus the control arm. In addition, we will compare adherence rates at months 2 and 6. Depending on the availability of drug susceptibility tests, we will compare the rates of MDR-TB. To understand the impact of the intervention on the treatment outcomes and the potential for adoption and scaling of the intervention, we will explore the perceptions and experiences of patients and care providers towards the MHI. Finally, we will determine the uptake and adherence to the intervention. We will consider the successful receipt of a reminder as a proxy for the utilization of the technology. Therefore, we will determine the proportion of successful calls in the intervention and control arms.

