### Sample size determination

Based on results from a randomized controlled trial in Kenya that demonstrated a 9% increase in TB treatment success following the use of SMS [12], we hypothesize that the interactive voice response platform will lead to at least a 6% higher impact as compared to SMS reminder treatment success (i.e., a 15%-point difference compared to the control arm). A retrospective cross-sectional study of routine data on HIV/TB co-infected patients from the Uganda National Tuberculosis and Leprosy Program reported lost to follow-up rates of 3.5% and 16.6% in urban and rural settings, respectively [7]. The rate of lost-to-follow at the three TB clinics was approximately 11.8%. Therefore, assuming an 11.8% lost-to-follow-up rate, this study would require a minimum of 274 (137 patients per arm) patients to demonstrate a 15% increment in treatment success with a power of 0.8 and precision of 0.05.

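### The economic endpoint is worded as one ratio with two stacked denominators, and the two sections that define it disagree on the second unit

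*Protocol article*

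**What the plan says.** The Research objectives section of the protocol article lists a secondary objective: "To determine the cost-effectiveness of the intervention". Two later sections define the measure that serves it.

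- Trial endpoints: "incremental costs per additional DALY averted per percentage point increase in treatment success in the intervention versus the control arm".
- Cost-effective analysis: "incremental costs per additional DALY averted per percentage increase in treatment success".

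The analysis section then describes the model. It is a decision analysis comparing the digital intervention with standard of care. Its inputs are the probabilities of cure and of treatment completion, taken from the trial for the intervention and from national TB reports for the control. The primary endpoint is built from the same two components: "treatment success is a composite outcome, comprising treatment completion and cure in patients with clinically and bacteriologically diagnosed TB, respectively".

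The article names no cost-effectiveness threshold and gives no numerical cost-effectiveness result. Table 2, which lists the analyses of the quantitative outcomes, has no economic row, so these two sentences are the only definitions of the measure.

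**The concern.** An incremental cost-effectiveness ratio has one difference in cost over one difference in effect. Here the cost difference is followed by two effects in succession, DALYs averted and the gain in treatment success, with no *and* or *or* between them. Read literally, the instruction is to divide by the first and then by the second.

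Three things follow from that reading:

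- The result does not have the unit of a cost per DALY, so it cannot be placed beside such figures for other interventions without being converted back.
- The two denominators overlap. The modelled DALYs are driven largely by cure and completion, and those are what treatment success is made of.
- The second divisor is not fixed, because one section says percentage point and the other says percentage. These are different quantities unless control success is 100%.

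The stake is interpretation. The article says that the trial aims to influence TB policy and that programme cost at scale will be modelled. An ill-formed unit cost could be misread in that setting.

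**Working it through.** There is no plan figure to reproduce, because the article gives no cost or DALY estimate. The check is therefore one of algebra and units.

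**Inputs**

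- d, gain in treatment success: 15 points, from the Sample size determination section ("a 15%-point difference compared to the control arm").
- C, incremental cost per 100 patients: not given. Assumed 10,000, range 2,000 to 10,000.
- k, DALYs averted per additional treatment success: not given. Assumed 3, range 1 to 5.
- D, DALYs averted per 100 patients: taken as k × d for illustration.

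**Formulas**

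- Cost per DALY averted = C / D
- Cost per percentage point = C / d
- Ratio as written (percentage-point wording) = (C / D) / d

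**Step 1: factor against cost per DALY.** (C / D) divided by [(C / D) / d] equals d. The ratio as written is smaller than cost per DALY by exactly the gain in points, whatever C and D are. At the planned effect the factor is 15. This step does not need D to be proportional to d.

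**Step 2: numbers with C = 10,000 and k = 3 (assumed)**

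| Gain d | D | Cost per DALY | Cost per point | Ratio as written |
|---|---|---|---|---|
| 15 | 45 | 10,000/45 = 222 | 10,000/15 = 667 | 222.2/15 = 14.8 |
| 7.5 | 22.5 | 10,000/22.5 = 444 | 10,000/7.5 = 1,333 | 444.4/7.5 = 59.3 |

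When the effect halves, each proper ratio doubles, but the ratio as written rises fourfold (59.3/14.8 = 4). Over the assumed ranges of C and k, at d = 15, cost per DALY runs from 27 to 667 and the ratio as written from 1.8 to 44.4.

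**Step 3: direction.** With D = k × d, the ratio as written is C / (k × d²). For a harmful effect, d = −10, cost per DALY is 10,000/(−30) = −333, while the ratio as written is −333/(−10) = +33.3. The sign of the effect is lost. This result and the fourfold change in step 2 do rest on proportionality. They are only approximate for the model described, whose control probabilities come from national reports.

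**Step 4: the unit of the second divisor.** If percentage means a relative increase, the divisor depends on control success, which the sample size section does not state. For a 15-point gain:

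| Control success (assumed) | Relative increase | Ratio as written (222.2 / increase) |
|---|---|---|
| 60% | 15/60 = 25.0% | 8.9 |
| 70% | 15/70 = 21.4% | 10.4 |
| 80% | 15/80 = 18.75% | 11.9 |

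Under the percentage-point wording the same data give 14.8. The two sections therefore lead to different numbers.

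**The case against.** The strongest reply is that this is a missing conjunction. The rest of the economic section describes a conventional evaluation: WHO guidance, a decision model and discounting ("All costs and DALYs derived from the models will be discounted at 3%, and a 5-year horizon will be used"). No step describes dividing the model output by the gain in success. On that view cost per DALY averted and cost per point gained were both intended, and nothing is divided twice. This is probably what was meant. It does not repair the text, because neither section separates the two ratios and these sentences are the only definitions given. The full protocol, a supplementary file not shown here, may be clearer. The article nevertheless states the measure, so this is not detail merely left to another document.

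A reader might infer that the plan counts exactly the same effect twice. The documents do not support that. The endpoint's gain is the intervention arm against the trial's control arm, whereas the model takes its control probabilities from national reports. The model also adds phone-coverage scenarios of 72% and 100%, years of life lost, and a Markov model for HIV co-infected patients. Modelled DALYs and the trial's gain overlap heavily but are not identical.

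A reader might also infer that the measure can never be compared with a threshold, or that it will make the intervention look cheaper than it is. Both go too far. No threshold is named, and multiplying by the gain recovers cost per DALY. The figure misleads only if someone takes it for a cost per DALY. For a positive gain below one point it would be larger than cost per DALY, not smaller.

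Nor does the repetition in two sections prove intent, since a badly formed phrase can be carried from one section to another.

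**Conclusion.** The point holds as a wrongly stated secondary endpoint. Both definitions stack two effect denominators on one cost difference, and they disagree on the second unit.

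If computed as written, the result is in currency per DALY per point and is not an incremental cost-effectiveness ratio. For any gain above one point it is numerically smaller than cost per DALY by a factor equal to that gain, which is 15 at the planned effect. The factor assumes literal computation with the percentage-point wording in the Trial endpoints section. Under a relative-percentage reading it depends on a control rate that is not stated. The second division largely, but not wholly, re-uses the effect already contained in the DALYs.

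The currency figures above are illustrations only. The primary endpoint, its analysis, the sample size and the data collection are not touched.

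**What to change.** In both the Trial endpoints and the Cost-effective analysis sections, replace the single phrase by two named ratios:

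1. Incremental cost per DALY averted, as the main measure.
2. Incremental cost per additional patient with treatment success, or per percentage point of treatment success.

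Use *percentage point* in both sections wherever an absolute difference is meant. The cost is one sentence in each of two sections. The planned model and the data to be collected already supply everything needed for both ratios.

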### Description of the proposed mobile health intervention

The technology to be evaluated in this study is Call for Life-TB (CFL-TB^TM)^, a software that is based on open-source mobile technology for community health (MoTeCH) [42]. MoTeCH was initially developed by the Grameen Foundation and the University of Southern Maine with the support of Janssen, the Pharmaceutical Companies of Johnson and Johnson. It was designed as a community MHI platform to improve treatment compliance in patients in LMICs [42, 43]. We then adapted and evaluated the technology to support people living with HIV in Uganda and named it Call for Life ^TM^ (CFL) [34]. CFL-TB uses interactive voice response (IVR) or short messaging service (SMS) to communicate with PLHIV via mobile phones [34]. This prototype, “Call for Life-Uganda”, was iteratively adapted to design CFL-TB, a technology tailored to address the needs of patients with TB. The needs of patients with TB were enumerated through discussions with health workers and patients at IDI HIV/TB clinics. The software was sequentially upgraded, and the subsequent versions were reviewed by end-users at each stage. End-users (study staff and patients with TB) reviewed the software for suitability and suggested changes. Overall, the changes were aimed at optimizing the usability and security of the software. Participants in the intervention arm will receive standard of care plus CFL-TB enhanced TB care, and those in the control arm will receive standard of care.

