### Randomization, blinding, and allocation concealment

At baseline, participants will be randomly assigned (1:1 ratio) to either the intervention or control arms (Fig. 2). The study statistician generated study allocation slips for participants for each study site using and these are then enclosed in sealed opaque envelopes. The number of cards allocated per study site will be equal to the enrolment target assigned to the study site. The allocation slips will indicate either the intervention or the control arm. The study arm will be allocated by drawing one envelope by a participant from a closed envelope box. Patients will randomly pick and open an envelope and they will be allocated a study arm that is indicated on the enclosed card. Since the opaque envelopes will be used and drawn from a closed opaque box, the allocation sequence is concealed from the recruiting study staff. We will maintain screening and enrolment logs at each study site to ensure that there is no bias in randomization and enrolment. Due to the study design involving voice reminders to participants, it is not possible to blind participants. However, the analyzing statistician will be blinded to the allocated arms.

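### The cost-effectiveness model sets the trial's intervention arm against national TB reports, so the effect in its ICER is not the randomised one

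*Protocol article*

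**What the plan says.** All references are to the protocol article.

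- **Model and inputs.** Cost-effective analysis describes a decision model built "to compare the cost-effectiveness of digital intervention versus standard of care". Its probabilities of cure and completion "will be obtained from the study (for intervention) and national TB reports (for control arms").
- **Economic endpoint.** Trial endpoints defines the measure as "incremental costs per additional DALY averted per percentage point increase in treatment success in the intervention versus the control arm".
- **Available comparator.** Under Randomization, blinding, and allocation concealment, "participants will be randomly assigned (1:1 ratio) to either the intervention or control arms". Under Description of the proposed mobile health intervention, "those in the control arm will receive standard of care". Table 1 schedules the same sputum tests and the same cost-effectiveness questionnaire in both arms.
- **Years of life lost (YLL).** Cost-effective analysis obtains YLL by "subtracting the median age at death from TB from the estimated average life expectancy at birth for Uganda", with a separate Markov model for HIV co-infected patients. It also says that costs and DALYs are discounted at 3% and that "a 5-year horizon will be used".

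**The concern.** The trial has a concurrent randomised arm receiving the very comparator that the model needs, yet the model takes that comparator's cure and completion probabilities from elsewhere. The trial population is selected: adult phone owners willing to follow study procedures, without critical illness, drug-resistant TB, TB meningitis or osteoarticular TB (Inclusion criteria, Exclusion criteria). It is also followed more actively than routine care need be: staff track missed visits (Participant withdrawal and post-trial care), and GeneXpert is scheduled at months 5 and 6 (Table 1). The trial's control arm shares all of these features. A national reporting population need not.

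The effect entering the ICER would therefore mix the effect of the calls with the effect of being a trial patient, and nothing in the described model separates the two. Cost-effectiveness is a stated secondary objective, and the Dissemination plan foresees policy briefs to the national TB programme, so the result is meant to be used.

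**Working it through.** The plan states no ICER and no success rate for the trial control arm or the national population, so there is no figure to reproduce. The check compares the two contrasts algebraically and then illustrates the difference.

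**Notation**

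- pI, pC: success probabilities in the trial's intervention and control arms.
- pN: success probability from national reports.
- d = pI − pC: the randomised effect.
- b = pN − pC: the mismatch between national and trial control rates.

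**Contrasts**

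- Measure under Trial endpoints: pI − pC = d.
- Model under Cost-effective analysis: pI − pN = (pI − pC) − (pN − pC) = d − b.

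The two agree only if b = 0. No adjustment of the national figures to the trial population is described.

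**Effect on the ICER.** Assume that incremental cost is fixed and that DALYs averted are proportional to the difference in success. The ICER is then proportional to 1/difference, and the model's ICER is the randomised one multiplied by d/(d − b).

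**Inputs.** d = 15 points is the planned difference in Sample size determination. d = 9 points is the upper end of the SMS effects cited under Study hypothesis. d = 0 is the case of no effect. All values of b are assumptions.

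| d (points) | b (points) | Increment used, d − b | ICER factor, d/(d − b) |
|---|---|---|---|
| 15 | −10 | 25 | 15/25 = 0.60 |
| 15 | −5 | 20 | 15/20 = 0.75 |
| 15 | 0 | 15 | 1.00 |
| 15 | +5 | 10 | 15/10 = 1.50 |
| 15 | +10 | 5 | 15/5 = 3.00 |
| 9 | −5 | 14 | 9/14 = 0.64 |
| 9 | +5 | 4 | 9/4 = 2.25 |
| 9 | +10 | −1 | increment changes sign |
| 0 | −5 | 5 | apparent gain of 5 points from no effect |

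With both arms taken from the trial, b drops out and the factor is 1.00 for any effect above zero.

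**YLL.** Let T be age at death. Life expectancy at birth is E[T]. For a person who has already reached age a, expected age at death is E[T | T > a], which is never below E[T] and exceeds it once some deaths occur before a. Remaining life expectancy at a is E[T | T > a] − a, whereas the plan's formula gives E[T] − a. For people who die as adults, the formula therefore understates years lost. The amount depends on a life table and on the age at death, neither of which the article gives, and it would be reduced by the 3% discounting.

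**The case against.** **National rates suit a national model.** The sentence on inputs follows text on phone coverage of 72% and 100% and precedes the use of the prevalence survey for national patient numbers. It can be read as describing a scale-up projection, with the economic endpoint itself left intact. That is fair as to purpose, and a national baseline is legitimate in such a projection. It does not rescue the inputs, because the plan pairs the trial arm's absolute probability with an external control rate; it does not apply the randomised effect to the national baseline. Nor does it describe a base case using the trial's control arm.

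**Reach.** A reader might infer that the randomised comparison is discarded altogether, or that the scale-up decision would rest on a non-randomised contrast. The article does not support either. Only the cure and completion inputs of one secondary objective are affected, and the hope of scale-up is tied to clinical effectiveness, which the randomised analyses assess.

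**Size and direction.** The national reports are not at hand, and whether they could be restricted to comparable patients is unknown. Selection and tracking make a bias in favour of the intervention plausible, but this cannot be shown. This objection stands.

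**YLL and horizon.** Understating YLL is conservative where the intervention averts deaths, and HIV co-infected patients are handled by another model. Both points stand. A reader might also infer that a 5-year horizon contradicts a YLL formula with no such limit. The text does not say whether the horizon bounds the period of implementation or the life-years counted, and years lost through deaths within five years can properly extend beyond it. It is an ambiguity, not a demonstrated error.

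**Conclusion.** The point holds for the model's cure and completion probabilities. Followed as written, the plan would produce an ICER whose effect is d − b instead of d, which is not the intervention-versus-control-arm measure under Trial endpoints. This does not depend on the size of b, since the described model cannot separate treatment effect from population difference.

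The magnitude is illustrative only: a factor of 0.75 or 1.50 for an assumed 5-point mismatch at the planned 15-point effect, given fixed incremental cost and DALYs averted proportional to success. The article supplies no value of b.

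The YLL formula is a secondary point. Its direction is established for adult deaths outside the HIV Markov model, but no percentage should be attached to it. The horizon needs clarification only.

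**What to change.** 1. **Base case.** Take cure and completion probabilities for both arms from the trial, with uncertainty derived from the trial data.
2. **National scale-up scenario.** Use national rates as the baseline and apply the trial's randomised effect to them. Label this as a scenario and keep it separate from the base case.
3. **YLL.** Outside the HIV Markov model, replace the subtraction from life expectancy at birth with remaining life expectancy at the age of death. State whether the 5-year horizon limits the implementation period or the life-years counted.

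The cost is a few sentences and a change of model inputs. The first two changes need no new data collection, because outcomes and the cost questionnaire are already scheduled in both arms; the third needs a life table. Enrolment, sample size and the clinical analyses are untouched.

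### Years of life lost for patients without HIV are taken as life expectancy at birth minus median age at TB death, which understates the loss per death and, if deaths are averted, raises the cost per DALY averted

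*Protocol article*

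**What the plan says.** Under Trial endpoints, the economic endpoint is a secondary one: "we will determine the incremental costs per additional DALY averted", set against the gain in treatment success.

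Under Cost-effective analysis, the YLL averted "will be calculated by subtracting the median age at death from TB from the estimated average life expectancy at birth for Uganda". The closing sentence of that section returns to the same input. Burden-of-disease estimates are to supply the DALY "weights for those patients with TB and life expectancy at birth".

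Three other statements in the section limit or surround the rule:

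- HIV: "Regarding the determination of YLL for HIV co-infected patients, a Markov model for ART-experienced PLHIV will be fitted".
- Discounting and horizon: "All costs and DALYs derived from the models will be discounted at 3%, and a 5-year horizon will be used".
- Model inputs: a decision-analysis model takes probabilities of cure and treatment completion, from the trial for the intervention and from national reports for the control. For the number of patients, "We will use the national TB prevalence survey [38] to estimate the number of patients with TB nationally".

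The article gives no value for life expectancy, age at TB death, YLL or DALYs.

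**The concern.** Life expectancy at birth averages over everyone born, including those who die in infancy, childhood and early adulthood. The trial enrols adults aged 18 or older, and a patient who dies of TB at a given age has already survived all that earlier mortality. The years forgone are the expectation of life remaining at that age. Subtracting the age from expectancy at birth gives a smaller number.

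This is a formula that the article states, and it names the input twice, so it cannot be read as detail left to a fuller document. YLL feed the DALYs averted, which form the denominator of the cost-effectiveness result. The section links that result to scale-up, and the dissemination plan aims to influence national TB policy. A denominator that is too small makes the intervention look less cost-effective than it is, provided that it averts deaths.

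The same sentences leave two smaller points open. The subtraction gives years for one death, although it is labelled as YLL averted. The section also does not say what the 5-year horizon does to years lost after a death.

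**Working it through.** **Reproduction.** The article states no YLL or DALY figure, so there is none to reproduce. The check is on direction, which needs no outside figure, and on size, which does.

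**Direction.** Let T be age at death in the population life table, e(0) = E[T] expectancy at birth, and e(x) remaining expectancy at age x.

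- Splitting on survival to x: e(0) = P(T ≤ x) · E[T | T ≤ x] + P(T > x) · (x + e(x)).
- Rearranged: e(x) − (e(0) − x) = P(T ≤ x) · (x + e(x) − E[T | T ≤ x]).
- The bracket is positive, because everyone in the last term died by age x. The right side is therefore zero only if nobody dies before x, and positive otherwise.

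So e(0) − x never exceeds e(x). The rule can only understate years lost per death.

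**Size, simple illustration.** All three inputs are assumptions: e(0) = 63, age at TB death x = 40, e(40) = 30 with a range of 28 to 35. The plan's rule gives 63 − 40 = 23 years.

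| Assumed e(40) | Rule ÷ e(40) | Shortfall, undiscounted | e(40) discounted at 3% | Shortfall, discounted |
|---|---|---|---|---|
| 28 | 23/28 = 0.82 | 18% | 19.04 | 12% |
| 30 | 23/30 = 0.77 | 23% | 19.89 | 16% |
| 35 | 23/35 = 0.66 | 34% | 21.81 | 23% |

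Discounting is mid-year: PV(n) = 1.03^0.5 × (1 − 1.03^−n)/0.03. For the rule, PV(23) = 16.69. The central comparison is 16.69/19.89 = 0.84. As the plan discounts at 3%, the last column is the relevant one.

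**Size, wider check.** This uses an assumed Gompertz–Makeham life table with e(0) of 58, 63 or 68, under-5 mortality of 3%, 6% or 10%, constant hazard 0.002 and slope 0.085. For median ages at death of 30 to 50:

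- Undiscounted, the shortfall is about 6 to 14 years per death, or 14% to 63%.
- With continuous discounting at 3%, it runs from 1 − 22.7/24.4 = 7% (e(0) 68, under-5 mortality 3%, age 30) to 1 − 7.1/16.1 = 56% (e(0) 58, under-5 mortality 10%, age 50).
- At e(0) = 63, under-5 mortality 6% and age 40, the discounted values are 16.6 against 20.7, about 20% too few.

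**Effect on the ratio.** If YLL in patients without HIV were the only health effect, cost per DALY averted would be overstated by 19.89/16.69 = 1.19, or 19%, in the central illustration. Years lived with disability and the Markov component for HIV co-infected patients do not use this rule as stated, so they can alter the effect on the total.

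**Unit.** The rule returns one number of years, the same in both arms. It becomes YLL averted only when multiplied by deaths averted.

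**The case against.** The strongest reply is about scope. Cost-effectiveness is a secondary endpoint, YLL are one part of the DALY, and HIV co-infected patients are modelled separately. All of that stands. A reader might infer that the whole DALY endpoint is wrong, but the article supports only a biased YLL component in patients without HIV. The bias also works against the intervention when deaths are averted, so it does not flatter the case for scale-up.

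A reader might also infer that the 5-year horizon contradicts the subtraction. In the illustration, a death cut off at 5 years counts for at most 4.65 discounted years, against 16.7 under the rule. But the sentence says only that DALYs are "discounted at 3%, and a 5-year horizon will be used". A horizon can bound when costs and deaths occur while crediting later life-years to those deaths, and on that reading the two agree. The horizon is ambiguous; no contradiction is shown.

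Nor does the article show that deaths are left out. The decision model may supply them, and the full protocol is not at hand. What remains is a label that does not match a per-death quantity.

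Finally, a reader might infer that the rule produces negative years for older patients. It uses one median age and is not applied death by death, so it turns negative only if that median exceeds life expectancy at birth. Nothing in the article suggests this.

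None of these replies touches the choice of expectancy at birth.

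**Conclusion.** The point holds in this limited form. For patients without HIV, the stated rule understates years of life lost per TB death. The direction holds for any life table with mortality before the age of death. If the intervention averts deaths, cost per DALY averted is overstated to a degree that depends on how much of the DALY total comes from this component.

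The size rests on assumptions, because the article gives no figures. At death at 40 with expectancy at birth of 63, the central shortfall is 23% undiscounted and about 16% at the planned 3% discount. It is larger if the median age at death is higher. The primary endpoint and trial conduct are unaffected. The per-death label and the meaning of the horizon need clarification but are not shown to be errors.

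**What to change.** In the section Cost-effective analysis:

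1. Replace life expectancy at birth with age-specific remaining life expectancy at the age of TB death, taken from a named life table. Make the same change in the closing sentence on burden-of-disease inputs.
2. Call this quantity years lost per death. Obtain YLL averted by applying it to the deaths averted that the decision model yields, and name the source of the death probabilities. Keep the planned model: summing trial deaths by age in each arm would rest on what are probably few deaths among 137 patients per arm.
3. State whether the 5-year horizon truncates years lost after a death or only bounds when costs and deaths occur. Report the other reading as a sensitivity analysis.

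The cost is a few sentences of economic-analysis text and a life-table lookup. No new participant data and no change to trial conduct are needed.
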